#### Secondary outcome measurement

Secondary outcomes include the mean change in pain intensity (0–10 numeric pain ranting scale) before and immediately after each protocol section. The measurement (pre and post intervention) will be conduced by a researcher blinded to patient allocation ([name]).

#### EEG recording and analysis

The EEG record will be done before and immediately after each protocol section.

EEG bipolar data will be collected from 26 scalp electrodes (Brain Wave II EEG, Inc., São Paulo, São Paulo) placed according to the International 10–20 system (Fp1, Fp2, F7, F3, Fz, F4, F8, FC3, Fcz, FC4, T3, C3, Cz, C4, T4, CP3, Cpz, CP4, T5, P3, Pz, P4, T6, O1, Oz, O2) [24, 25]. This system aims to standardize the electrodes arrangement in specific areas of the scalp surface regardless the size of the skull (Fig. 4). Electrooculogram data will be recorded from electrodes placed above and below the left eye orbit and at the lateral canthus of both eyes.

**Fig. 4 Fig4:**
[figure not shown]
International 10–20 system [28]

The EEG will be recorded with the eyes closed and opened, and each recording will last 2 min. During the exam, the participants will be in seated position (16). The participants will be given only two verbal commands: to open and close their eyes.

A computerized Fourier analysis of the EEG waves will be made, using the Brain Wave Analyzer Software. The signal will be sampled at 500Hz rate, and filtered with a 1–50 Hz band-pass filter. The signal will be filtered to display alpha frequency (8–13 Hz). Electrode impedance will be kept below 5KΩ, and the ground electrode placed at the Fpz location.

### Statistical analysis and sample size

#### Baseline and outcome data

The baseline characteristics will be shown as the mean ± SD for continuous data (i.e., participant’s age and duration of back pain), and n (%) for categorical data (i.e., gender). To analyze the baseline characteristics, we will perform a One Way analysis of variance, or a Kruskal-Wallis test for continuous data if the data are normally distributed. Shapiro-Wilk test will be used to test data normality. The primary and secondary (EEG and pain) outcomes will be analyzed by 3 × 2 mixed-effects model (group [CV4 - CV 4 sham - Control] x time [pre and post]) to repeated data measures for each continuous outcome variable, we will also assesses if the allocation order will interfere in results, for thus we’ll analyze the order of allocation of CV4 (1^st^, 2^nd^ or 3^rd^) x pre values (CV4 – CV4 sham – Control) at the 3^rd^ exposition, using a one-way Anova or Kruskal-Wallis test. When the analysis of variance indicates significant differences among groups, a post-hoc test (Bonferroni test) will be used to separate the differences between groups before and after the intervention period. Data will be analyzed using Prism 6 software for Mac OS X, and a significance level of *p* ≤ 0,05 will be considered to all variables.

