#### Sample size

The sample size was calculated considering: (1) the two-way analysis of variance (ANOVA); [26] three groups; (3) type I error = 5 % (2-sided); (4) type II error = 20 %; (5) the power of the statistical test = 80 %; and (6) effect size = 20 %. The effect size was obtained considering: (I) the results from the pilot study of Miana et al. [16], which demonstrated a effect of 26 % (pre to post intervention) in the group that received the CV4 technique and (II) Cohen’s *d* which considers 20 % a small effect to calculate sample size and power analysis [27, 28]. Then, it was determined a total of 81 subjects. This calculation was performed in G Power 3 program, version for Mac OS X.

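### The ANOVA/Kruskal-Wallis rule for baseline comparisons is reversed as printed, and the order check offers the same two tests with no rule of its own

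*Protocol article*

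**What the plan says.** All the relevant text is in the protocol article, under Statistical analysis and sample size, in the subsection Baseline and outcome data.

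- **Baseline characteristics.** These are summarised first: "The baseline characteristics will be shown as the mean ± SD for continuous data", with age and duration of back pain as the examples. For the comparison, the plan names a one-way ANOVA, "or a Kruskal-Wallis test for continuous data if the data are normally distributed".
- **Normality criterion.** "Shapiro-Wilk test will be used to test data normality".
- **Order check.** Participants are grouped by whether CV4 came first, second or third, and their pre-session values at the third exposure are compared, "using a one-way Anova or Kruskal-Wallis test". No condition for choosing between the two is attached.
- **Outcomes.** "The primary and secondary (EEG and pain) outcomes will be analyzed by 3 × 2 mixed-effects model". Neither the normality test nor the choice between ANOVA and Kruskal-Wallis is tied to this model.

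**The concern.** One-way ANOVA is derived for normally distributed errors. Kruskal-Wallis is the rank-based alternative for when that assumption is doubtful. The baseline sentence puts the normality condition on the rank test. By elimination, ANOVA is left for data that fail Shapiro-Wilk.

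This is the only test-selection rule in the article, so a reader looking for the rule behind the order check has nowhere else to turn. The order check is the one analysis described that looks directly at whether sequence affects the results of this three-period crossover with a 7-day washout. If ANOVA were applied there to strongly skewed pre-session values, a real order effect would be somewhat easier to miss. If no rule applies, the analyst may choose between two p-values after seeing the data.

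**Working it through.** **Step 1: what the text fixes.** The point is about wording, and the plan gives no figure to reproduce. Each use of the two tests is set out below.

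| Analysis | Tests named | Condition printed | Status |
|---|---|---|---|
| Baseline characteristics | ANOVA or Kruskal-Wallis | Kruskal-Wallis if normal | Reversed |
| Order check at third exposure | ANOVA or Kruskal-Wallis | None | Inherits the reversed rule, or has none |
| EEG and pain outcomes | 3 × 2 mixed-effects model | Not applicable | Not affected |

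**Step 2: inputs for sizing the consequence.**
- Total sample size 81 (section Sample size). Balanced groups of 81 / 3 = 27 are an assumption.
- Alpha 0.05, two-sided (section Sample size).
- The article gives no distribution or size of order effect. Those used below are assumptions.

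**Step 3: type I error** (simulation, 4,000 replicates, three groups of 27).
- Normal data: ANOVA 4.5%, Kruskal-Wallis 4.5%.
- Lognormal data, log-SD 1: ANOVA 3.8%, Kruskal-Wallis 4.8%.

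Neither test exceeds 5%, whichever way round the rule is applied.

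**Step 4: power on normal data, where the printed rule sends the analyst to Kruskal-Wallis.**
- The large-sample efficiency of Kruskal-Wallis relative to ANOVA is 3/π = 0.955.
- One group shifted by 0.75 SD: ANOVA 80.0%, Kruskal-Wallis 77.7%, a loss of 80.0 − 77.7 = 2.3 points.
- One group shifted by 0.8 SD: ANOVA about 86%, Kruskal-Wallis about 84%, a loss of about 2 points.

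**Step 5: power on skewed data, where the printed rule leaves ANOVA.** The data are lognormal, with one group shifted by 0.8 log-SD on the log scale. Kruskal-Wallis depends only on ranks, so its power does not change with log-SD and stays at about 83 to 84%.

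| Log-SD | ANOVA, upward shift | ANOVA, downward shift |
|---|---|---|
| 0.6 | 81% | 74% |
| 0.8 | 76% | 67% |
| 1.0 | about 70% | 56% |

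For the upward shift the loss runs from about 84 − 81 = 3 to about 83 − 70 = 13 points. It is larger for a downward shift, up to about 83 − 56 = 27 points. The size therefore depends on assumptions that the article cannot settle.

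**Step 6: which variables could be that skewed.** A variable confined to an interval has an SD of at most half the interval's width. Alpha is defined as 8–13 Hz (section EEG recording and analysis), so the log-SD of peak frequency is at most (ln 13 − ln 8)/2 = ln(1.625)/2 = 0.4855/2 = 0.24. Log-SDs of 0.6 to 1.0 are therefore out of reach for it. They are conceivable for alpha power, which enters the order check, and for duration of back pain, which enters the baseline comparison. Pain intensity is bounded at 0–10, so a lognormal model does not describe it well.

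**The case against.** **It is a language slip that no statistician would follow.** That is probably true. The article has other slips of English, and the intended meaning is easy to guess. It is still the operative rule in the published analysis text, and it says the opposite of what was presumably meant. This limits the severity but does not make the sentence correct.

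**The order check is not stated to use the wrong test.** This stands. A reader might infer that the check is assigned the wrong test as written. The condition sits in a sentence confined to baseline characteristics, and the order check carries none. Carrying the reversal over is an inference, and a selection rule left unstated in a condensed article would not be a finding by itself. It is mentioned here because the only rule a reader could borrow is the reversed one.

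**ANOVA is never expressly assigned to non-normal data.** This is also correct. That follows only by elimination.

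**The baseline tests decide nothing.** Every participant is to receive all three conditions, and the plan attaches no decision to the baseline comparison. EEG and pain are also recorded before each session, with pre/post time in the outcome model, so each condition is read against its own session baseline. It would overstate the case to call the order check the only protection against carry-over.

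**The simulation inputs are assumed.** They are. Stratified simple randomization does not guarantee groups of 27, and the skew used cannot apply to peak frequency. The figures show an order of magnitude only.

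**Conclusion.** The baseline test-selection rule is wrong as printed and should be corrected. For the order check, the supportable statement is that it either inherits a reversed rule or has no rule.

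Two stronger conclusions are not supported. The first is that the primary or secondary results are compromised: they come from a mixed-effects model that this sentence does not govern. The second is that false-positive rates are inflated: both tests stay at about 5% or below. Kruskal-Wallis on normal data is a valid test and only slightly less efficient.

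What remains is lost power in the baseline comparisons and, if the rule is carried over, in the order check. The loss is about 2 to 3 points on normal data. It is about 3 to 13 points on markedly skewed variables, under assumed lognormal data with log-SD 0.6 to 1.0, an upward shift of 0.8 log-SD in one group, and groups of 27. A downward shift would cost more. No figure stated in the article changes. Minor severity.

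**What to change.** Reword the baseline sentence to: one-way ANOVA if the data are compatible with normality, Kruskal-Wallis if they are not. Add that the same rule governs the comparison of pre-session values at the third exposure, so that its test is also chosen in advance. This costs one or two sentences. No data collection, procedure, sample size or outcome analysis changes.

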### Participants randomization and allocation

After participants selection, randomization will be performed using a computerized random number generator through the stratified simple randomization method of a software program (Excel, Microsoft Office 2008) for sequence generation. Sequentially numbered, opaque, sealed assignment envelopes will be delivered at the Hospital and the researcher will open one envelope in front of the participant; each envelope contains a concealed allocation number.

The three researchers performing the interventions will not have access to the order of allocation file. The allocation electronic file will be password-protected and only the fourth researcher will have the password to access it (ST).

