### Intervention

All participants will receive three interventions at the Outpatient Rehabilitation Service of the University Hospital of Brasília (room F49, blue hall), respecting a 7-days washout interval and the same appointment time, which may be scheduled between 8 and 11 a.m.

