### Measurements

#### Primary outcome measurement

The mean change in peak alpha frequency (PAF) will be the primary outcome measure to assess the effects of CV4 technique on nonspecific chronic low back pain. PAF is a measure derived from EEG analysis, and it is defined by two parameters: (1) its occurrence on the frequency axis; and 2) its amplitude on the power density axis. The participants assessment (EEG) and the results statistical analysis will conducted by a blinded researcher ([name]).

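### The three-visit crossover is analysed without a period term, and the gate for post-hoc tests does not name the group x time interaction that matches the primary outcome

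*Protocol article*

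**What the plan says.** The Intervention section makes this a full crossover: "All participants will receive three interventions", at visits separated by a seven-day washout. Under Primary outcome measurement, "The mean change in peak alpha frequency (PAF) will be the primary outcome measure", so the quantity of interest is a within-session difference.

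Under Baseline and outcome data, "The primary and secondary (EEG and pain) outcomes will be analyzed by 3 × 2 mixed-effects model", whose factors are "group [CV4 - CV 4 sham - Control] x time [pre and post]) to repeated data measures for each continuous outcome variable". Time here means before and after one session, not visit 1, 2 or 3.

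Order is treated separately: "we’ll analyze the order of allocation of CV4 (1^st^, 2^nd^ or 3^rd^) x pre values (CV4 – CV4 sham – Control) at the 3^rd^ exposition", by one-way ANOVA or Kruskal-Wallis.

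The step to pairwise tests reads: "When the analysis of variance indicates significant differences among groups, a post-hoc test (Bonferroni test) will be used", and its purpose is "to separate the differences between groups before and after the intervention period".

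Under Participants randomization and allocation, the order comes from the "stratified simple randomization method of a software program". The strata are not named, and nothing says that the six possible orders are balanced.

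**The concern.** Two features of the stated analysis do not fit the design.

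1. **Visit is missing.** Novelty of the EEG session, habituation or regression of pain can make the first visit differ from the third. A crossover analysis normally removes this with a period effect. Without one, any visit effect on the pre-post change stays in the residual. If more participants happen to receive CV4 first than sham first, part of it also enters the CV4-sham contrast in that trial.

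2. **The gate is not tied to the outcome.** A difference among groups in a group x time model can mean the group main effect, which averages pre and post, or the group x time interaction, which compares changes. Only the interaction corresponds to the primary outcome. Pre-session values cannot carry that session's effect, so a main-effect gate dilutes the effect and can respond to chance differences before treatment.

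Two analysts following this text could test different terms and reach different conclusions on the primary outcome.

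**Working it through.** **Inputs.** From the article: 81 participants, three conditions, pre and post recordings, two-sided alpha of 5%. It gives no variance components, so those below are assumptions: total SD 1, CV4 effect 0.2 at the post recording only, sham and control equal, and participant/visit/residual variance shares p/v/r = 0.6/0.2/0.2. Here v is a random session component, not a visit trend.

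**The plan's own figure.** For a fixed-effects ANOVA with f = 0.20, 2 numerator df, alpha 0.05 and power 0.80, the noncentral F gives a total of 244 observations. 81 x 3 = 243 is in line with this. The number 81 is only an input here.

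**Order imbalance under simple randomization.**
- CV4-first minus sham-first: variance = 81 x (1/3 + 1/3) = 54, so SD = 7.35.
- Chance of a gap of 10 or more: 2 x P(Z > 9.5/7.35) = 2 x P(Z > 1.29), about 20%.
- A gap of 10 carries 10/81 = 12% of any first-visit effect on the change into the contrast.
- Mean visit number, CV4 minus sham: the per-participant difference is ±1 in four orders and ±2 in two, so its variance is (4 x 1 + 2 x 4)/6 = 2. The SD of the mean is sqrt(2/81) = 0.157 visits.

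**What a visit effect does to the contrast of changes.** Here the assumed SDs are participant 1.0, visit 0.5 and recording 0.5. With a linear trend d per visit in the change itself:

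SD = sqrt((4 x 0.25 + 2d²)/81)

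- d = 0: 0.111
- d = 0.25: 0.118
- d = 0.50: 0.136

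Simulation (2,000 trials per scenario, simple randomization to six orders) agrees. Power of the group x time test at an effect of 0.25, which is about 0.2 of the total SD (0.25/sqrt(1.5) = 0.20):

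| Trend in change per visit | No period term | Period term |
|---|---|---|
| 0 | 0.62 | 0.61 |
| 0.25 | 0.56 | 0.61 |
| 0.50 | 0.45 | 0.62 |

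At an effect of 0.35 and a trend of 0.50, power is 0.76 without the term and 0.90 with it. With no treatment effect, the mean CV4-sham contrast of changes lay between -0.003 and +0.005, and the rejection rate of the interaction test under simple randomization was 0.042 to 0.060. A visit shift common to pre and post left the SD of the change contrast as it was (0.109 with a shift of 0.5 per visit, 0.113 without).

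**What the gate does** (shares 0.6/0.2/0.2, no visit trend).
- Group main effect: the contrast is (0 + 0.2)/2 = 0.1. SE = sqrt(2(v + r/2)/81) = sqrt(0.6/81) = 0.086. For the omnibus test, lambda = 81 x (0.1² x 2/3)/0.3 = 1.8 on 2 and 160 df, giving power of about 20%.
- Contrast of changes, CV4 minus sham: the contrast is 0.2. SE = sqrt(4r/81) = sqrt(0.8/81) = 0.099. z = 2.01 and power is about 52%.
- Omnibus interaction: lambda = 81 x (0.2² x 2/3)/0.4 = 5.4, giving power of about 53%.

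With shares from 0.5/0.3/0.2 to 0.7/0.1/0.2, the main-effect gate has about 16% to 29% power. The contrast of changes stays at 52%, because its SE depends only on r. At r = 0.3 it falls to about 38%.

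**Pre-value as covariate** (same shares). Within participant, pre and post each have variance v + r = 0.4 and covariance v = 0.2. The residual variance is 0.4 - 0.2²/0.4 = 0.3, so SE = sqrt(2 x 0.3/81) = 0.086 (0.087 in simulation) against 0.099.

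**The case against.** The strongest reply is that the planned model already contains the right term. A 3 x 2 group x time model includes the interaction, and the outcome section makes the primary measure a change. A reasonable analyst would test the interaction, and nothing would then be diluted. This stands. A reader might infer that the plan does halve the treatment effect; the text supports only that it fails to exclude this.

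A reader might also infer that visit effects bias CV4 against sham. The article does not support that either. Order is randomized, so the contrast is unbiased over repeated trials, and a shift common to pre and post cancels in the change. What remains is chance imbalance and extra residual variance, and only if the change itself varies by visit. No such trend is documented, and the 0.50 per visit used above is large beside the treatment effect.

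A third tempting reading is an inflated type I error. If participant were the only random effect, the group main effect would reject a true null in about 12% to 19% of trials under the shares above. This needs both the main-effect reading and a random structure that the article does not state and may leave to a fuller document.

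The article does not ignore order: it plans a test at the third exposure. But that test examines pre-session values only and changes no estimate of treatment. Finally, a contrast of raw changes is valid, so adjusting for the pre-value is a gain in efficiency and not the repair of an error.

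**Conclusion.** The concern holds in a limited form. For a three-visit crossover, the stated factors omit period, the order check does not replace it, and the gate for pairwise tests does not identify the term that corresponds to the primary outcome.

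The factor of one half under a main-effect gate is algebraic, given no effect before the session. The power figures (about 20% against 52%) and the gain from a period term rest on assumed variance shares and visit trends. The order-imbalance figures need only n = 81 and equal-probability simple randomization; the unnamed strata could change them somewhat.

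This is a SHOULD-FIX with moderate confidence: a loss of precision and an ambiguity in the primary test, with no systematic bias shown.

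**What to change.** - Name the CV4-minus-sham contrast of session change (from the group x time term) as the primary test, with its 95% CI, so that it does not depend on an unspecified group difference. Keep Bonferroni for the other pairs.
- Add period (visit 1 to 3) as a fixed effect on the change, with participant and visit within participant as random effects. If pre and post are kept as separate rows, this means including period x time.
- Optional efficiency gain: model the post-session value with condition, period, that session's pre-value and the participant's mean pre-value. Under the assumed shares the SE falls from 0.099 to about 0.087.
- If the randomization list has not yet been made, use permuted blocks over the six condition orders.

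The cost is 2 degrees of freedom for period, revised analysis wording, a mixed-model program and, where still possible, a new list. No further data are needed.

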### Exclusion criteria

Participants suffering wiil be excluded if they present: (I) secondary chronic low back pain (ankylosing spondylitis, infections, malignancy, nephrolithiasis, pyelonephritis, aortic aneurysm, disease of the pelvic organs and gastrointestinal tract); (II) fever, chills, sweating, relate of weight loss superior of 5 % in the last 2 months without a clear cause, asthenia, anorexia; (III) cardiovascular and respiratory symptoms such as chest pain, dyspnea and cough; (IV) headache, dizziness, lightheadedness, fainting, tremors, dysarthria and aphasia; (V) surgery on the spine; (VI) diagnosis of any neurological, cardiac, respiratory and rheumatic disease; (VII) regular use of drugs with effects on the central nervous system (stimulants or depressors of CNS, examples: anxiolytics, anti-depressives, neuromodulators, etc.); (VIII) previous manual therapy treatment before data collection (in a four-eight weeks period of time); (IX) signs of nerve root involviment.

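### The only stated order check compares third-visit pre-values between different people, so it has low power for small-to-moderate carryover and leaves better data unused

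*Protocol article*

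**What the plan says.** All references are to the protocol article.

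- **Baseline and outcome data.** The EEG and pain outcomes go into a 3 × 2 mixed-effects model whose only named terms are condition (CV4, sham, control) and time (pre, post). On order, the article says "we will also assesses if the allocation order will interfere in results". The method given is a comparison of pre-values at the third exposure across the position of CV4 (first, second or third), by one-way ANOVA or Kruskal-Wallis. No covariate is named.
- **Same section, baseline characteristics.** The rule for choosing between those two tests reads "or a Kruskal-Wallis test for continuous data if the data are normally distributed".
- **Intervention.** Every participant receives all three conditions, "respecting a 7-days washout interval and the same appointment time".
- **Exclusion criteria.** People are excluded for "previous manual therapy treatment before data collection (in a four-eight weeks period of time").
- **Primary outcome measurement, and EEG recording and analysis.** The primary outcome is the mean change in peak alpha frequency. EEG is recorded before and immediately after each session.
- **Sample size.** "it was determined a total of 81 subjects". The stated inputs include "type I error = 5 % (2-sided"), "the power of the statistical test = 80" per cent and "effect size = 20" per cent. They concern the main comparison. No power is given for the order check.

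**The concern.** A three-period crossover draws its strength from comparing each person with themselves. The order check gives that up. Each participant has one CV4 position, so the test sets different people against each other and carries the full between-person variance.

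It also leaves out two useful sets of data that will already be recorded:

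- The second-visit pre-values. People who had CV4 first are then 7 days past it.
- Each person's first-visit pre-value, which precedes any session.

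Since the main model names only condition and time, this test is the one stated safeguard against order and carryover effects. If it is weak, a null result says little. The question matters because, with balanced orders, half of the sham and control sessions come after CV4, and the article gives no reason for the length of the washout.

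**Working it through.** **What the plan's own figure covers.** The article gives no power for the order check, so there is no figure to reproduce for it. The 81 belongs to the main comparison, and its stated inputs do not settle it. With f = 0.20, α = 0.05 and 80% power, a three-group between-subject ANOVA needs 244. A group-by-time interaction needs 124, 82 or 64 at within-person correlations of 0, 0.35 or 0.5. A total near 81 thus needs a correlation that the article does not state. That is a separate matter; 81 is taken as given here.

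**Inputs**

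- N = 81 and α = 0.05 (Sample size).
- k = 3 sets by CV4 position (Baseline and outcome data).
- n = 81/3 = 27 per set. This is an assumption: the article gives no allocation ratio and names simple randomization, which does not guarantee 27.
- Shift d in SD units of the pre-value. The article gives no carryover size, so a range is shown.

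**Power of the stated check.** Suppose only the set that had CV4 second (7 days earlier) is shifted by d. The set means are 0, d, 0, the grand mean is d/3, and the squared deviations sum to (1 + 4 + 1)d²/9 = 2d²/3. Then λ = 27 × 2d²/3 = 18d², equivalently f = d√2/3, with F on 2 and 78 df.

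| d (SD) | λ = 18d² | power |
|---|---|---|
| 0.2 | 0.72 | 0.106 |
| 0.3 | 1.62 | 0.184 |
| 0.4 | 2.88 | 0.300 |
| 0.5 | 4.50 | 0.445 |
| 0.7 | 8.82 | 0.744 |
| 0.8 | 11.52 | 0.855 |

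Power of 80% is reached at d = 0.746 (f = 0.35).

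Three variations:

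- If the CV4-first set (14 days past) keeps half the shift, the means are d/2, d, 0 and λ = 27 × d²/2 = 13.5d². Power is 9% at 0.2 SD and 35% at 0.5 SD; the detectable shift is 0.86 SD.
- With 22 per set (an illustrative loss of 15/81, about 19%), the detectable shift is 0.83 SD, or 0.96 SD in the half-shift pattern.
- For a difference as large as the trial's own effect size read as f = 0.20, λ = 81 × 0.04 = 3.24 and power is 33%.

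**Gain from the first-visit pre-value.** Adjusting for a covariate correlated r with the third-visit value multiplies the error variance by 1 − r², so the detectable shift becomes 0.746 × √(1 − r²). The article gives no r, so a range is shown.

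| r (assumed) | detectable shift (SD) | power at 0.4 SD |
|---|---|---|
| none used | 0.75 | 30% |
| 0.5 | 0.65 | 39% |
| 0.7 | 0.53 | 54% |
| 0.8 | 0.45 | 70% |
| 0.9 | 0.33 | 94% |

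**Gain from all three visits.** A within-person model of the three pre-values, with period and a term for CV4 at the previous visit, has a detectable shift of 0.35 / 0.28 / 0.23 / 0.16 SD at r = 0.5 / 0.7 / 0.8 / 0.9. This assumes six balanced sequences and carryover to the next visit only. It is close to the model proposed below but not identical, so it shows scale only.

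**Exposure.** With 27 per position, CV4-first people have two later sessions, CV4-second people one and CV4-third people none: 54 + 27 + 0 = 81 of the 2 × 81 = 162 sham and control sessions. Each falls 7 or 14 days after CV4, a shorter gap than the 28 to 56 days named in the entry criterion.

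**What the check can see.** It uses pre-values only. If carryover adds c to both pre and post in a session, the change is (post + c) − (pre + c) = post − pre, so c drops out. If carryover instead alters how a person responds to the next session, the change itself moves. A test of pre-values need not show that.

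**The case against.** **Low power is not blindness.** A reader might infer that the check cannot detect any realistic carryover. The article does not support that: it gives no carryover size, and power is 74% at 0.7 SD and 86% at 0.8 SD. What stands is low power for small-to-moderate shifts.

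**The two time windows can both be followed.** A reader might see 7 days against four to eight weeks as a contradiction. One is an entry rule on previous manual therapy of unspecified type and amount; the other spaces single study sessions. The article gives no reason for either length. What remains is an unexplained tension.

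**Each session has its own baseline.** A reader might infer that residual CV4 effect biases the contrasts toward zero. The outcome is pre-to-post change, so a level shift that lasts through the session largely cancels, and the direction of any remaining bias cannot be derived from the article. This objection largely succeeds. It leaves carryover that alters the next response, which the check does not examine.

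**The plan does not gate on this test.** Nothing says that a non-significant result will be taken as proof of no carryover, or that the primary analysis depends on it. That is correct; the point concerns only what the result could support.

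**The reversed Kruskal-Wallis clause is minor.** It sits in the sentence on baseline characteristics and looks like a dropped word. It is the only selection rule given for the pair of tests that the order check also names, so it deserves correcting, but it adds nothing to the carryover argument.

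**A separate analysis plan may hold more.** It may, but the order check is a stated choice and not a detail left open.

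**Conclusion.** The concern holds in a limited form. As specified, the order check is a between-person test at one visit. It reaches 80% power only at a shift of about 0.75 SD in one set, and would miss a 0.4 SD shift about seven times in ten. A null result would not show that carryover is absent. The power figures rest on an equal split of 81, no dropout and a shift in one set; unequal sets or dropout would be expected to lower them. The size of the gain from adjustment depends on a correlation that the article does not give, and at r = 0.5 it is modest for the third-visit comparison alone.

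The main contrasts are not shown to be biased. The remaining risk is carryover that changes the response to the next session, which no stated analysis addresses. The 7-day interval is unexplained beside the exclusion window, but the two do not contradict each other.

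**What to change.** 1. Replace the third-visit test with a mixed model of the visit-2 and visit-3 pre-values on time since CV4 (not yet, 7 days, 14 days) and period, adjusted for the visit-1 pre-value. Report the carryover estimates with 95% confidence intervals.
2. Add a sensitivity analysis of the primary change outcome with period and prior-treatment terms. This addresses carryover that alters the next response, including carryover from sham.
3. Correct the test-choice sentence so that Kruskal-Wallis applies when the data are not normally distributed.
4. Reconcile the washout in the Intervention section with the manual-therapy window in the Exclusion criteria, and give the reason for the difference. No interval is proposed here.

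Items 1 to 3 cost analysis wording and a little more analysis, on measurements already scheduled. Item 4 needs a protocol clarification. No extra participants or visits are required.
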